Currently, the etiology of sarcopenia remains a subject of global debate, with consensus yet to be reached. The scholarly community widely acknowledges that sarcopenia in the elderly stems from a confluence of factors, rather than a singular cause. As a chronic condition that accelerates the aging process, the pathogenesis of sarcopenia is intricate and multifaceted. Aging and sedentary lifestyles rank among the primary contributors to sarcopenia, leading to a reduction in skeletal muscle mass, fibrotic infiltration, and adipose tissue replacement within muscle fibers, as well as atrophy of type II fibers and compromised neural control over muscle function ^[5]^. Research from both domestic and international sources indicates that elderly individuals with insufficient physical activity constitute a high-risk demographic for the development of sarcopenia ^[6]^. As the body ages, there is a notable decline in skeletal muscle mass and muscular strength among the elderly, which restricts their physical activity. This limitation not only impedes normal physical exertion but, over time, also precipitates a decline in health and functional capacity.

In 2010, the European Working Group on Sarcopenia in Older People (EWGSOP) delineated sarcopenia into three distinct stages: pre-sarcopenia, sarcopenia, and severe sarcopenia. Pre-sarcopenia is characterized solely by a reduction in muscle mass. Sarcopenia extends beyond this to include a decline in muscle strength or function. This stratification is instrumental in formulating clinical intervention strategies and objectives.

The pathogenesis of sarcopenia in the elderly is attributed to both intrinsic and extrinsic factors. Intrinsic factors encompass age-related skeletal muscle atrophy, structural alterations within the musculature, mitochondrial dysfunction, degeneration of motor nerves, and hormonal decline. Extrinsic factors include malnutrition and a lack of physical activity [7][8][9]. Given the deleterious side effects associated with hormone therapy, its application in clinical settings is constrained. Consequently, nutritional and exercise interventions have emerged as the cornerstone treatments for sarcopenia, representing fundamental strategies in managing this condition in the elderly population ^[9]^.

Traditional Chinese medicine (TCM) health care practices, such as Baduanjin and Tai chi Chuan, are quintessential to China’s rehabilitative exercise regimen. These ancient techniques are revered for their capacity to harmonize the internal organs, meridians, and the flow of qi and blood, thereby fostering spiritual well-being and mental fortitude. Each gong method is distinct; for instance, Tai chi Chuan is known for its intricate and elaborate movements, which may pose a challenge for the layperson to master.

In contrast, Baduanjin stands out as a holistic and self-contained fitness system that has been cherished for generations. It is celebrated for its body-strengthening effects and is a staple in the realm of traditional health-promoting exercises. Baduanjin aligns seamlessly with the principles of kinesiology and physiology ^[10]^, offering an accessible, safe, and efficacious workout that transcends common barriers such as time, location, and cost. It is readily embraced by patients due to its ease of learning and adaptability to various conditions. Moreover, Baduanjin’s philosophy of balancing yin and yang to heal the spirit further enhances its therapeutic value, making it particularly beneficial for patient rehabilitation. As a form of low- to medium-intensity aerobic exercise ^[11]^, Baduanjin is ideally suited to the national context of China. Research by Zou L et al. ^[12]^ substantiates the efficacy of Baduanjin exercises, highlighting improvements in quality of life, sleep patterns, trunk stability, grip strength, and trunk flexibility. This evidence underscores the significance of Baduanjin as a culturally congruent and scientifically validated approach to health and rehabilitation in China.

1. **Purposes**

Utilizing the Short Physical Performance Battery (SPPB) as a metric, this investigation aims to scrutinize the clinical outcomes of a consistent regimen of Baduanjin exercises in geriatric patients diagnosed with sarcopenia. Concurrently, it endeavors to assess the impact of the Baduanjin technique, rooted in traditional Chinese medicine qigong, on the life quality and safety of these patients. The objective is to devise a standardized Baduanjin exercise protocol tailored for sarcopenia, thereby pioneering an exercise rehabilitation paradigm that resonates with China’s national ethos. This study aspires to furnish a robust theoretical framework that will underpin the practical application and widespread dissemination of this approach in the management of sarcopenia among the elderly. Furthermore, it seeks to contribute a scholarly foundation for the endorsement and implementation of Baduanjin in the realm of geriatric sarcopenia.

1. **Methods**

**3.1 Participants**

**3.1.1 Diagnostic criteria**

The diagnostic criteria set forth by the Asian Working Group for Sarcopenia ^[13]^ are as follows:

- A: SMI (Skeletal Muscle Index): This is determined using Bioelectrical Impedance Analysis (BIA) and should be less than or equal to 7.0 kg/m^2^ for males and less than or equal to 5.7 kg/m^2^ for females.
- B: Muscle strength (Handgrip Strength): The strength threshold is less than 28 kg for males and less than 18 kg for females.
- C: Physical performance

6-metre walk: <1.0 m/s

or 5-me chair stand test: ≥12 s

or Short Physical Performance Battery: ≤9

A diagnosis of sarcopenia is confirmed when both criteria A and B or A and C are met. It's important to note that these criteria are specifically tailored to the Asian population and take into account the distinct body composition profiles prevalent in this demographic.

**3.1.2 Inclusion criteria**

- Participants should be elderly individuals aged between 60 and 84 years, who conform to the established diagnostic benchmarks for sarcopenia.
- Candidates must be amenable to engaging in comprehensive body composition analysis, handgrip strength assessment, 6-meter walk time evaluation, and completing pertinent questionnaires.
- Prospective participants ought to possess the ability to ambulate independently, whether unassisted or utilizing supportive devices.
- Individuals should demonstrate the capacity to safely execute exercise regimens as prescribed by medical professionals.
- Participants must express their willingness to partake in the study, adhere to the randomized intervention protocol, and provide signed informed consent.

**3.1.3 Exclusion criteria**

- Individuals exhibiting a 6-meter walking speed of less than 1.0 m/s, or those who require 12 seconds or longer to complete 5 sit-ups, or have an SPPB (Short Physical Performance Battery) score greater than 9 points.
- Patients afflicted with severe pathologies that influence muscle and bone metabolism, including but not limited to renal disease, malignant tumors, cerebrovascular accidents, advanced liver disease, severe diabetes mellitus, thyroid disorders, and parathyroid diseases.
- Those currently undergoing treatment with medications known to impact muscle and bone metabolism, such as glucocorticoids, androgens, oestrogens, thyroid hormones, among others.
- Individuals who have a consistent routine of physical activity, defined as engaging in high-intensity physical activity for at least 15 minutes daily, or participating in plyometric training at least twice weekly in the 12-week preceding enrollment.
- Participants with significant cognitive deficits, as evidenced by a score below 20 on the Simple Intelligence Scale.

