**9.2 Quality control of study participant enrolment**

The recruitment protocol for the study was executed with precision by specialized recruiters who adhered strictly to the established inclusion and exclusion criteria. Candidates who fulfilled all the inclusion criteria while not meeting any of the exclusion criteria were systematically included in the study and sequentially assigned a study number. Conversely, individuals who did not meet the qualifying criteria were excluded. The recruiters meticulously documented each exclusion, noting the total number of exclusions along with the specific reasons for each disqualification.

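### The first exclusion bullet in 3.1.3 bars patients at the same gait and chair-stand cut-offs that qualify them as sarcopenic in 3.1.1, while its SPPB limb points the opposite way

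*Combined protocol and SAP*

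**What the plan says.** Section 3.1.1 of the combined protocol and SAP defines sarcopenia by three criteria: A (low skeletal muscle index), B (low grip strength) and C (poor physical performance). The combination rule is: "A diagnosis of sarcopenia is confirmed when both criteria A and B or A and C are met". Criterion C has three alternatives. The gait alternative is "6-metre walk: <1.0 m/s"; the one for rising from a chair is "or 5-me chair stand test: ≥12 s"; the one for the total score is "or Short Physical Performance Battery: ≤9". Section 3.1.2 ties entry to that diagnosis by admitting people "who conform to the established diagnostic benchmarks for sarcopenia".

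The first bullet of section 3.1.3 excludes "Individuals exhibiting a 6-meter walking speed of less than 1.0 m/s, or those who require 12 seconds or longer to complete 5 sit-ups". The third limb of the same bullet concerns the total score and reads: "or have an SPPB (Short Physical Performance Battery) score greater than 9 points".

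Sections 9.1 and 9.2 leave the screeners no discretion. Section 9.2 states: "Candidates who fulfilled all the inclusion criteria while not meeting any of the exclusion criteria were systematically included". Both sections say that exclusions were recorded with their reasons.

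The SPPB total, scored 0 to 12, is the primary outcome (section 8.2, Table 1).

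**The concern.** An exclusion criterion may narrow a diagnosed population, but this bullet has no consistent direction. Its first two limbs remove poor performers at exactly the cut-offs by which 3.1.1 calls them sarcopenic. Its third limb removes good performers.

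Two things are at stake. If the bullet was followed as written, the trial enrolled an unusual subgroup: people who walk and rise from a chair quickly and still have a low SPPB. In them, gains on the primary outcome can come almost only from balance. Section 8.2 presents the chair stand as the measure of lower-body strength, and the comparator includes squats, lunges and calf raises (section 7.2). A leg-strength benefit in that arm would barely register. If the bullet was not followed as written, the documents do not say what rule replaced it, and a reader cannot tell who was enrolled.

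**Working it through.** **Step 1. Set the two rules side by side.**

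| Measure | Qualifies under C (3.1.1) | Excluded (3.1.3) | Must hold to enter, read literally |
| --- | --- | --- | --- |
| 6 m gait speed | <1.0 m/s | <1.0 m/s | ≥1.0 m/s |
| Five repetitions | ≥12 s | ≥12 s | <12 s |
| SPPB | ≤9 | >9 | ≤9 |

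The limbs of the exclusion are joined by *or*, so an entrant must clear all three. Anyone who does has SPPB ≤9 and so meets C by that route. With criterion A, the diagnosis is satisfied. The eligible set is therefore not logically empty.

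**Step 2. Translate to SPPB sub-scores (Table 1).** Assumptions: the five sit-ups are chair stands, and usual pace is similar over 4 m and 6 m.

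- Gait: at 1.0 m/s, 4 m takes 4/1.0 = 4.0 s. The top category is under 4.82 s, which is 4/4.82 = 0.83 m/s. So gait scores 4/4.
- Chair stand: under 12 s falls either below 11.20 s (4 points) or in 11.20–13.69 s (3 points).
- Balance: a total ≤9 needs balance ≤ 9 − 4 − 3 = 2 when chair stand is 3, and ≤ 9 − 4 − 4 = 1 when chair stand is 4.

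**Step 3. Count patterns.** Three sub-scores of 0–4 give 5³ = 125 patterns. Those with a total of 10 or more number 6 + 3 + 1 = 10, which leaves 115 with SPPB ≤9. The patterns that survive the bullet are:

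| Gait | Chair stand | Balance | Total | Headroom: gait / chair / balance / total |
| --- | --- | --- | --- | --- |
| 4 | 3 | 0 | 7 | 0 / 1 / 4 / 5 |
| 4 | 3 | 1 | 8 | 0 / 1 / 3 / 4 |
| 4 | 3 | 2 | 9 | 0 / 1 / 2 / 3 |
| 4 | 4 | 0 | 8 | 0 / 0 / 4 / 4 |
| 4 | 4 | 1 | 9 | 0 / 0 / 3 / 3 |

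That is 5 of 115, with totals 7 to 9.

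**Step 4. Relax the pace assumption.** If the 4 m walk can score 3 despite a 6 m speed of ≥1.0 m/s, gait 3 adds 4 patterns (chair 3, balance 0–3) and 3 patterns (chair 4, balance 0–2). The count becomes 5 + 4 + 3 = 12 of 115, with totals 6 to 9 and balance ≤3.

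**Step 5. Compare with the planning figures.** Section 4 plans on 9.83 ± 1.85 against 8.39 ± 2.52, a difference of 1.44, from older adults at high risk of falls. Scores confined to 7–9 cannot have a standard deviation above about half the range, (9 − 7)/2 = 1. For 6–9 the bound is (9 − 6)/2 = 1.5. These bounds apply to baseline scores, while the planning values read as scores after a 24-week intervention. So this raises doubt about the fit of the planning population and does not disprove the planning values.

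**Step 6. Do the possible repairs agree?** Dropping the gait and chair-stand limbs would leave SPPB ≤9 as the only performance limit. Reversing their inequalities would instead require gait <1.0 m/s and five repetitions in ≥12 s as well as SPPB ≤9. That population shares no patient with the literal one. The text does not show which was meant.

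**The case against.** Several stronger readings are tempting, and the documents do not support them.

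- *The diagnosis requires slow gait or slow chair stand, so nobody can qualify.* It does not. They are two of three alternatives within C, and A with B suffices without C.
- *The eligible population is almost empty.* The documents give no prevalence or screening yield, and a count of score patterns is not a share of patients. The balance item is itself unclear: section 8.2 describes a side-by-side stand, while Table 1 lists standing on one foot. If the harder stance was used, low balance scores would be less rare.
- *Balance is the only deficit of those admitted.* All have low muscle mass, some may have weak grip, and three of the five patterns score 3/4 on chair stand.
- *The primary outcome is at its ceiling.* Total headroom is 3 to 5 points, against a planned between-group difference of 1.44. What stands is that nearly all of that room lies in balance.
- *Excluding A-with-B patients whose SPPB exceeds 9 is an error.* That limb is stated openly, and narrowing a diagnosed population is what an exclusion does. It needs confirming as intended, no more.

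The best defence is that this is a drafting slip that screeners saw through. That may be so, but sections 9.1 and 9.2 say the criteria were applied strictly, and no other section gives a different rule. The contradiction itself has no counter-argument in the documents.

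**Conclusion.** The point holds as an internal contradiction in the eligibility rule, and it must be fixed. Two of the three limbs of the first exclusion bullet repeat qualifying signs of criterion C at the same cut-offs, and the third runs the opposite way. This rests on the text alone.

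The consequence for the primary outcome is conditional. It assumes that the bullet was applied literally, that the sit-ups are chair stands, and that pace is similar over 4 m and 6 m. The range across the pace assumption is 5 to 12 of 115 patterns. How many real patients this covers cannot be derived from the documents, and whether the planning scores suit such a group is an open question.

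**What to change.** Reconcile sections 3.1.1, 3.1.2 and 3.1.3. Rewrite the first exclusion bullet so that its three limbs point in one direction and do not remove patients for the signs that qualify them. The sponsor must state which population is intended: whether the gait and chair-stand limbs were included by mistake or had their inequalities reversed, and whether the SPPB limit is meant to apply to patients who qualify by A with B. This review takes no position on which is right.

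Then check two sets of records against the clarified rule: the exclusion records described in 9.1 and 9.2, for patients wrongly turned away, and the baseline assessments, for patients wrongly enrolled. The exclusion records alone cannot show the latter. Report which rule was actually applied. Section 5 gives a recruitment window of July 2022 to August 2023, so if enrolment is complete, the clarification, record check and report are the essential actions.

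The cost is one amended or clarified bullet and a check of records already kept.

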**3.1.4 Suspension criteria**

- Should a participant express a desire to discontinue their involvement in the study at any point, their request will be honored, and they will be withdrawn from the clinical trial.
- Participants who are untraceable or fail to attend scheduled follow-up assessments will be considered lost to follow-up and subsequently withdrawn from the study.
- In the event that a participant develops new comorbidities, complications, or undergoes physiological changes during the study that render them unsuitable for continued intervention, they will be removed from the trial.
- If a participant’s health status significantly worsens during the study, potentially leading to a critical event, and the supervising physician deems it necessary to halt the clinical trial for the individual’s safety, the participant will be withdrawn from the study.

**3.1.5 Elimination criteria**

- Participants who are subsequently found to not fulfill the inclusion criteria after the commencement of the study will be excluded.
- Subjects who decline to participate in the prescribed examination and assessment protocol during the study will be withdrawn.
- Participants demonstrating suboptimal adherence, with cumulative exercise time falling below 80% of the prescribed amount, or those who consume medication that influences muscle or bone metabolism during the study period, will be considered non-compliant and thus removed from the trial.

1. **Sample size**

The prevalence of functional falls and fractures is a significant clinical concern and a severe consequence for patients with sarcopenia, stemming from the progressive loss of muscle mass and function. The Simple Physical Performance Measurement Scale (SPPB) serves as a pivotal efficacy indicator in this context. Drawing from extant literature ^[14]^, a 24-week exercise intervention in elderly patients with a heightened risk of falls yielded an SPPB score of 9.83 ± 1.85 in the experimental group, compared to 8.39 ± 2.52 in the control group. Employing a two-sided test with an alpha level (α) of 0.05 and a power (test efficacy) of 0.9, the calculated sample size for a single group is n = 35.6, which approximates to 36 participants. Consequently, the combined sample size for both groups amounts to 72 individuals. Factoring in a dropout rate of 20%, the total sample size required for this study is 90 cases, equating to 45 participants per group.

1. **Participant**

The proposed study aims to enroll 90 elderly patients with sarcopenia who visited the Hospital of Chengdu University of Traditional Chinese Medicine between July 2022 to August 2023. The process for inclusion involves a meticulous screening of candidates at the outpatient clinic. Potential participants are to be thoroughly informed about the study’s objectives, procedures, and potential risks. Following this educational dialogue, those who meet the study criteria and express a willingness to participate will be asked to provide informed consent and sign the corresponding consent form.

1. **Randomization and Blinding**

The random allocation sequence was delegated to a specialized statistical analyst, who utilized the SAS 9.4 software (SAS, USA) to generate a series of random numbers ranging from 1 to 90. Subsequently, the analyst enumerated the eligible participants in sequential order of their enrollment and allocated them randomly in a balanced 1:1 ratio to either the Baduanjin exercise intervention cohort—hereinafter referred to as the ‘Baduanjin group’—or the resistance training comparator arm—hereafter denoted as the ‘control group’. The integrity of the randomization sequence was preserved by the study administrator, who remained uninvolved in participant recruitment, outcome evaluation, and statistical analysis. Upon completion of all initial assessments, participants were apprised of their group assignment via telephone.

Due to the nature of the intervention, it was impracticable to blind the study participants. Consequently, blinding was confined to the outcome assessment, data management, and statistical analysis phases. In lieu of explicit group identifiers, the designations ‘A’ and ‘B’ were employed on the case report forms to maintain anonymity. An independent statistical expert, external to the participant cohort, employed SAS software to create the blind base—a table of random numbers—which was subsequently safeguarded by the study administrator. The statistician tasked with data analysis remained uninformed about the specific intervention programs administered to each group. This blinding was only disclosed subsequent to the completion of all statistical analyses.

1. **Interventions**

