**7.5 Assessment of sports attendance**

The protocol for tracking attendance in your study is well-defined. Intervention supervisors are responsible for recording attendance at each training session. Participants who engage in the training for less than 20 minutes are marked as absent.

The attendance rate is calculated at the conclusion of the intervention period using the formula:

- % attendance=(number of training sessions attended / total number of training sessions planned)×100%

1. **Measure**

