**10.2 Data analyses**

Following an intention-to-treat (ITT) protocol, those whose cumulative time of exercise reaches 80% of the amount to be completed and not higher than 120% of that will be classified into per protocol set (PPS). Categorical variables will be presented as percentages or frequencies. As for continuous variables, normally distributed data will be described by mean ± standard deviation, while non-normally distributed data will be described using median [interquartile range (IQR)]. Baseline demographic descriptors and outcome measures wil be compared across groups by using analysis of variance for continuous variables and the $\chi$*^2^* (or Fisher exact) test for categorical variables. Within the scope of this investigation, the Generalized Estimating Equations (GEE) framework was employed to evaluate the impact of Baduanjin exercise on sarcopenia among the elderly cohort. GEE is a robust statistical approach designed to analyze correlated data or repeated measurements over time, rendering it particularly adept at accommodating incomplete datasets and multiple observational instances.Initially, an exhaustive data cleansing and encoding procedure will be undertaken to ascertain the precision and integrity of the dataset. Continuous variables will undergo a distributional analysis to discern the necessity of transformation to align with the normal distribution assumption. Categorical variables will be delineated through frequencies and percentages.The GEE model will incorporate temporal factors as a repeated measures variable, alongside other pertinent covariates that may influence the outcomes, such as age, gender, and baseline muscle mass index. The inclusion of interaction terms pertinent to time will facilitate an in-depth assessment of the longitudinal effects of Baduanjin exercise on sarcopenia. The model’s fit will be gauged using the Quasi-likelihood under the Independence model Criterion (QIC), with preference given to the model demonstrating the minimal QIC value. Additionally, a thorough examination of model residuals will be conducted to validate the adherence to underlying assumptions.Two-sided P values of less than 0.05 will be considered statistically significant. Analyses will be conducted using SPSS version 23.0 (IBM Corp) or GraphPad Prism version 7.0 (GraphPad Software).

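### Section 3.1.5 removes randomised participants on grounds that 10.2, under intention-to-treat, uses only to define the per-protocol set; this can bias the SPPB comparison

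*Combined protocol and SAP*

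**What the plan says.** Section 3.1.5 (Elimination criteria) lists grounds that apply once the study is under way:

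- Late-found ineligibility: "Participants who are subsequently found to not fulfill the inclusion criteria after the commencement of the study will be excluded".
- Declining assessments: "Subjects who decline to participate in the prescribed examination and assessment protocol during the study will be withdrawn".
- Low adherence, defined as "cumulative exercise time falling below 80% of the prescribed amount", or medication, described as "those who consume medication that influences muscle or bone metabolism during the study period". Both groups "will be considered non-compliant and thus removed from the trial".

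Section 3.1.4 (Suspension criteria) adds that people who cannot be traced or who miss a scheduled follow-up assessment "will be considered lost to follow-up and subsequently withdrawn from the study".

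Section 10.2 (Data analyses) opens its account of analysis sets with "Following an intention-to-treat (ITT) protocol, those whose cumulative time of exercise reaches 80% of the amount to be completed" and goes on, in the same sentence, to put those between 80% and 120% into the PPS. It does not say who makes up the ITT set. The model is GEE, chosen partly because it copes with incomplete data.

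Section 7.5 defines an attendance rate as sessions attended over sessions planned, with the rule that "Participants who engage in the training for less than 20 minutes are marked as absent". Sections 4 and 10.1 allow for 20% dropout.

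**The concern.** Sections 3.1.5 and 10.2 give the same 80% threshold two different consequences. Under 10.2 a participant below it leaves the PPS and stays in the ITT analysis. Under 3.1.5 that participant leaves the trial. Both cannot operate as written, and the choice decides who enters the primary analysis.

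Adherence and new medication are observed after randomisation. Participants know their allocation (section 6), and Baduanjin and resistance training are different programmes (7.1, 7.2), so the share removed, and the kind of person removed, may differ by arm. The groups compared would then no longer be the groups that were randomised, and part of any SPPB difference could come from selection. Late-found ineligibility is a weaker source of bias, since eligibility is fixed before allocation. It belongs in the same repair because it too takes randomised people out of an analysis labelled ITT.

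Leaving the conflict unresolved also leaves the analysis set open to choice after the results are known.

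**Working it through.** **1. The two sections side by side.**

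| Participant | Under 3.1.5 | Under 10.2 |
|---|---|---|
| Exercise time below 80% | removed from the trial | outside the PPS; in an ITT analysis |
| 80% to 120% | stays | in the PPS |
| Above 120% | stays | outside the PPS; in an ITT analysis |
| Takes muscle- or bone-active medication | removed from the trial | not mentioned; in an ITT analysis |
| Found ineligible later | excluded | not mentioned; in an ITT analysis |

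If the 3.1.5 column is applied first, nobody below 80% is left. The lower PPS limit then does nothing, and on adherence the two sets differ only in the third row.

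**2. When the rule acts.** Sections 7.1 and 7.2 prescribe 3 sessions × 24 weeks = 72 sessions of 60 minutes, or 72 hours. Eighty per cent is 0.8 × 72 = 57.6 hours, so the rule applies once more than 14.4 hours are missed. It depends on behaviour accumulated over the whole intervention.

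**3. Possible size of the bias (illustration).** The documents give no removal rates, so these are assumed.

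- SD, from the two SDs in section 4: √((1.85² + 2.52²)/2) = 2.21.
- Planned difference, from section 4: 9.83 − 8.39 = 1.44.
- Assumed: no true effect; the least adherent fraction p of an arm is removed; adherence and SPPB are jointly normal with correlation ρ = 0.3 in both arms.

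Removing the lowest p raises that arm's mean by ρ × SD × m(p), where m(p) = φ(z_p)/(1 − p):

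- m(0.10) = 0.1755/0.90 = 0.195
- m(0.20) = 0.2800/0.80 = 0.350
- m(0.30) = 0.3477/0.70 = 0.497

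The spurious difference is 0.3 × 2.21 × the difference in m:

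| Removed, arm 1 vs arm 2 | Bias at ρ = 0.3 | Share of 1.44 | Bias, ρ = 0.2 to 0.4 | Type I error, ρ = 0.2 to 0.4 |
|---|---|---|---|---|
| 20% vs 20% | 0 | 0% | 0 | 0.050 |
| 20% vs 10% | 0.10 | 7% | 0.07 to 0.14 | 0.052 to 0.058 |
| 30% vs 10% | 0.20 | 14% | 0.13 to 0.27 | 0.057 to 0.080 |

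Type I error uses a normal approximation with 45 randomised per group, less those removed, and a nominal two-sided 0.05.

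**4. The dropout allowance.** Section 4 gives 36/(1 − 0.20) = 45 per group. Neither section 4 nor 10.1 says whether the 20% includes removals under 3.1.5.

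**5. The measure behind the 80% rule.** Sections 3.1.5 and 10.2 state it in cumulative time. Section 7.5 defines only a count of sessions. No section says how cumulative time is to be computed.

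**The case against.** The strongest reply is that removal may mean only that a person stops taking part, not that data are deleted. Attendance is calculated at the end of the intervention (7.5, 9.3), about when the week-24 assessment falls, so a non-complier could well be measured. GEE can use the baseline and week-12 values of people who leave. This stands in part: a reader might infer that the week-24 SPPB of non-compliers is never obtained, and the documents do not support that. But they do not say that it is obtained or analysed either, and nothing ties the remark about incomplete data to participants removed under 3.1.5. Unweighted GEE also assumes data missing completely at random, which is hard to defend for removal on adherence.

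Four other stronger readings should be set aside.

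- *That the comparison is biased.* With equal removal and the same correlation in both arms the bias is zero. The supported wording is that removal can bias it.
- *That the bias could reach a third of the planned effect.* With 20% removed in each arm and correlations of opposite sign, the formula gives 2 × 0.3 × 2.21 × 0.350 = 0.46 points, or 32% of 1.44. Nothing in the documents suggests opposite signs; both arms exercise on the same 3 × 60 minute schedule.
- *That removals cut power from 90% to about 70%.* A further 10% to 20% off 36 leaves about 32 to 29 per group, with power 0.73 to 0.68 (noncentral t, SD 2.21). At that SD, 36 per group already gives only 0.78, so removals would cost about 5 to 9 points. The rest is a separate sample-size matter. If the 20% allowance already covers removals, there is no extra loss.
- *That the 80% rule cannot be measured.* The 20-minute rule implies some timing, sessions are overseen (9.3), and heart rate is monitored throughout (7.4). The gap is an unstated method.

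**Conclusion.** The contradiction between 3.1.5 and 10.2 is in the text and needs no assumption. Followed literally, 3.1.5 would make the ITT set one selected on post-randomisation behaviour, and no section keeps removed participants in follow-up or in the analysis.

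The size of the consequence is uncertain. Under the assumed rates the bias is modest, about 0.10 to 0.20 SPPB points at a correlation of 0.3, and it vanishes if removal and its relation to outcome are the same in both arms. These figures rest on assumed removal rates, an assumed correlation and an SD taken from section 4; they illustrate and do not predict. The point must still be fixed, because it determines the primary analysis population and the repair is cheap.

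**What to change.** 1. State in 10.2 that the primary analysis includes all randomised participants in the group to which they were allocated, regardless of adherence, medication or eligibility found later.
2. Use the 3.1.5 grounds to define exclusions from the PPS, not from the trial or the primary analysis.
3. Separate stopping the exercise programme from stopping outcome assessment. Stopping exercise remains the investigators' clinical decision, and the wording of 3.1.4 and 3.1.5 must be reconciled on it. Keep inviting participants to the 12- and 24-week assessments unless they withdraw consent.
4. State how missing SPPB values are handled, for example by weighting or multiple imputation, because unweighted GEE assumes data missing completely at random.
5. State how cumulative exercise time is computed for the 80% to 120% rule, for example from minutes logged per session.
6. State whether the 20% dropout allowance includes participants who would meet a 3.1.5 ground.

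If follow-up is already complete, analyse every randomised participant with data and report removals by arm and reason.

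The cost is amended wording, follow-up contact with people who stop exercising, and one more entry on the attendance record. The ITT estimate will also be diluted by non-adherence. If 10% to 30% do not adhere and keep 50% to 0% of the effect (assumed), the expected difference falls from 1.44 to between 1.44 × (1 − 0.10 × 0.5) = 1.37 and 1.44 × (1 − 0.30) = 1.01. Power with 45 per group analysed (normal approximation, SD 2.21) then falls from 0.87 to between 0.84 and 0.58.
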